# SYNOPSIS

| Sponsor/Sponsor-Investigator | [name]. [name]. (main contact person)  University Hospital Basel |
| --- | --- |
| Co-Principal-Investigators and US-Chair | [name], M.D., M.P.H. (US Chair)  Semmes Murphey Clinic and University of Tennessee Health Sciences Center |
| Title | ProSPective evaluation of the dIagnostic accuracy of siNe spiN non-contrast flat-dEtectoR CT (FDCT) imaging for the detection of intracranial hemorrhage in Stroke patients – an open labelled, multicenter, non-inferiority comparison of FDCT to multi detector CT (MDCT) with blinded assessment of outcome events |
| Short Title | SPINNERS |
| Clinical Investigation Plan, Version and Date: | Version 2.0 29.04.2024 |
| Registration: | Clincialtrials.gov: NCT05458908 and SNCTP |
| Category and its rationale: | According to Swiss legislation (Human research act (HRA)^5^ and Art 6 Clinical Trial Ordinance-MD (ClinO-MD)^2^) the clinical investigation is categorized as a clinical investigation concerning a medical device class A2, since the medical device under investigation is CE-certified, commercially available in Switzerland and it will be used within its intended use. As the additional performance of the non-contrast syngo DynaCT Sine Spin may not be clinical routine in a subgroup of subjects and in these subjects associated with excess radiation (up to 2.5 mSV, according to internal measurements and recent publications)^3, 6^ ,the clinical investigation is rated as A2. No contrast-media will be applied for the study.  US medical device classification Class 2. Minimal risk to subject (up to 2.5 mSv according to internal measurements and recent publications) |
| Name of the MD,  Unique Device  Identification (UDI),  name of the  manufacture | ARTIS icono biplane angiography system, model no.: 11327600, software version VE20 or higher with syngo application software, model no.: 11327667, version VE20D or higher with syngo DynaCT Sine Spin head imaging protocol.  UDI-DI ARTIS icono: 04056869063317  UDI-DI syngo application software: 04056869124162  US 510(k) Number:  ARTIS icono K201156  syngo application software K190780 |
| Stage of development | Post-market stage |
| Background and rationale | Stroke is one of the leading causes of mortality and disability worldwide. Mechanical thrombectomy became the gold-standard for the treatment of acute ischemic stroke due to large-vessel occlusions (LVO) after the publication of five large landmark trials.^7, 8^ However, as was shown by a post-hoc meta-analysis of these five trials clinical outcome is highly associated with the time from hospital admission to reperfusion.^9^ One possibility to substantially shorten this time span is the implementation of a direct to angiography approach. In this workflow both imaging and subsequent EVT is done in the angiography suite using non-contrast flat detector CT (FDCT) for the exclusion of an intracranial hemorrhage.^10^ We and other workgroups were already able to show in large patient series that such workflows dramatically reduce intra-hospital time delays (median reductions of more than 30 minutes) and are associated with improved patient outcomes.^11-14^ This workflow is mainly suitable for suspected stroke patients with disabling symptoms (National Institute of Health Stroke Scale (NIHSS) ≥ 7), since in this patient population the likelihood of a treatable LVO is substantially higher compared to patients with lower NIHSS scores.^15, 16^  One of the biggest hurdles for a large-scale implementation of a direct to angiography approach up to now is the ability to differentiate between ischemic and hemorrhagic stroke with FDCT. In earlier generations of angiography equipment, image deterioration due to artefacts and reduced image quality near the skull and the skull base limited the use of FDCT as a triage tool.^17^ However, in a recent study we reported very high sensitivity and specificity for the detection of intracranial hemorrhage with FDCT.^18^ Recently Siemens Healthineers introduced the new ARTIS icono angiography system with a new non-contrast syngo DynaCT Sine Spin protocol FDCT (from here-on in the CIP FDCT and non-contrast syngo DynaCT Sine Spin FDCT will be used synonymously), which should improve the quality and soft tissue resolution of native cranial FDCT scans especially in the posterior fossa and skull base.  Therefore, we aim to evaluate if non-contrast syngo DynaCT Sine Spin FDCT is non-inferior to non-contrast multidetector CT (MDCT) for the detection of intracranial hemorrhages. |
| Objective(s): | The primary objective is to evaluate if non-contrast FDCT imaging is non-inferior compared to non-contrast MDCT for the detection and exclusion of intracranial hemorrhages. Non-contrast FDCT imaging will be deemed non-inferior if both the lower bounds of the 95% confidence interval (CI) of the sensitivity and of the specificity are above 95% (pre-defined non-inferiority margins), using MDCT as the reference standard.  The secondary objectives are to determine the sensitivity, specificity, positive predictive value, and negative predictive value of non-contrast FDCT imaging for the detection of intracranial hemorrhage. The sensitivity (including its 95%-CI) for the detection of an intracranial hemorrhage within the subset of patients presenting with an isolated infratentorial intracranial hemorrhage will be reported separately. A further secondary objective is to determine the interrater agreement for non-contrast FDCT imaging regarding the occurrence of intracranial hemorrhage. |
| Outcome(s): | The primary outcome is the occurrence of intracranial hemorrhages (yes vs no) as assessed by a blinded core-lab. The primary outcome will be used to calculate the sensitivity and specificity of non-contrast syngo DynaCT Sine Spin imaging for the detection of intracranial hemorrhages.  There are no secondary outcomes. |
| Design: | Cross-sectional non-inferiority investigation with prospective open label data collection and blinded endpoint assessment. |
| Inclusion/Exclusion criteria: | Inclusion criteria:   - Informed Consent as documented by signature or fulfilling the criteria for emergency or deferral of consent - Patients with symptoms suggestive of stroke ischemic (NIHSS ≥ 7) or hemorrhagic stroke with a cranial non-contrast MDCT and a feasible non-contrast syngo DynaCT Sine Spin FDCT within 4 hours - Patient presenting within 24 hours of last seen well - Patients presenting directly to the treating hospital (i.e. mothership patients) OR transfer patients with the indication for repeated imaging according to the standard operation procedures of the treating hospital - Age above 18 years - Agreement of treating physician to perform non-contrast syngo DynaCT Sine Spin FDCT   Exclusion criteria:   - Severe metal artefacts on initial MDCT imaging - Planned invasive interventions between MDCT and FDCT scan - Clinical deterioration between MDCT and FDCT scan (i.e. an increase of the NIHSS of more than 4 points) - Evidence of an ongoing pregnancy prior to enrollment. A negative pregnancy test before enrollment is required for all women with child-bearing potential |
| Measurements and procedures: | All subjects will undergo non-contrast cranial MDCT and non-contrast FDCT imaging with a maximal time span of four hours between the two scans. Only patients in whom no invasive procedure is planned or performed in between the scans can be enrolled. Subjects will be enrolled based on clinical features (symptoms of the stroke) and according to a pre-defined number of needed hemorrhagic and non-hemorrhagic stroke patients. They will be recruited in a ratio of 1:1. This will be secured over an online enrollment system in which the investigator has to enter if a patient has a hemorrhagic (and location of hemorrhage) or non-hemorrhagic stroke. All sites must maintain screening logs.  To ensure compliance with the Protocol and adequate acquisition technique of the FDCT and MDCT at the respective site the first five cases from each site will be deemed as lead-in cases. Cases can be excluded and deemed as Screen Failures if they show clear evidence of (a) operator failure (for example due to clear artifacts due to objects in the field of view, wrong positioning of head, wrong acquisition protocol, severe motion artifacts, missing reconstructions) or (b) technical failure due to missing calibration of the scanner. The ultimate decision to exclude cases is made by the Independent Core Lab (under the supervision of [name]). In such a case it is the obligation of the Sponsor to perform retraining. Excluded cases will be replaced to ensure adequate power.  All non-contrast MDCT and FDCT scans will be rated by blinded readers, who were not involved in the original treatment or enrollment of the subjects on an individual basis in a core-lab (the core lab service will be provided by the Neurovascular Imaging Research Core, [name], University of California Los Angeles, Los Angeles, USA). The readers will be experienced in neuroimaging. All scans will be reconstructed in a standardized matter (i.e., fixed slice thickness 5 mm, distance 3 mm and angles – orbitomeatal) and randomized prior to evaluation. All MDCT scans will be read by one reader with no time-limit, while all FDCT scans will be read by six readers with a time-limit of 90 seconds (only applicable to the decision hemorrhage positive or negative). The reader of the MDCT scan will not be part of the six readers who read the FDCT scans. Each of the six readers will read all FDCT scans completely independent from the other readers, and they will not share any information.  The ground truth (i.e., if an intracranial hemorrhage is present) will be defined based on the MDCT readings according to the following procedure. If the readings of the clinical reader and the core-lab are consistent, this will be deemed as ground truth. In case they are inconsistent (i.e., at the clinic it is rated as hemorrhage positive and in the core-lab as hemorrhage negative or vice versa) a second independent core-lab consisting of a highly experienced neuroradiologist ([name], Inselspital Bern, Bern, Switzerland) will read the MDCT scan and review all available clinical data. Based on this information he will make a final ruling (i.e., define the ground truth for this patient, majority vote).  The FDCT readings of the six Core-Lab readers will be compared with the ground truth and based on this comparison they will be rated as true positive, true negative, false positive or false negative. These values will be calculated for each reader separately. In case most of the core-lab 1 readers (at least 5 out of 6) detects a hemorrhage on the FDCT scan, which according to the ground truth was hemorrhage negative the second core-lab will use all available clinical data to deduce if there is any evidence for the hemorrhage to have occurred between both scans. In this case the patient will be excluded from further analysis.  See table 1 for a detailed overview of all possible constellations.   \| Ground truth \| Core-Lab 1 \| Core-Lab 2 \| Final Result \| \| --- \| --- \| --- \| --- \| \|  \| FDCT \| Unblinded \| FDCT \| \| (+) \| (+) \| NA \| True (+) \| \| (-) \| (-) \| NA \| True (-) \| \| (+) \| (-) \| NA \| False (-) \| \| (-) \| (+) \| (-) \| False (+) \| \| (-) \| (+) \| (+) \| Hemorrhage occurred between scans \|   Table 1. Overview of possible outcomes  The results are used to calculate the sensitivity and specificity of the FDCT. |
| Interventions: | The examined intervention is a non-contrast cranial syngo DynaCT Sine Spin scan with an ARTIS Icono angiography system.  The intervention itself takes under 1 minute. The timespan from enrolment to the last investigation specific visit (the non-contrast syngo DynaCT Sine Spin) is 4 hours at max. |
| Control: | The control intervention is a non-contrast cranial MDCT (at least 64 slice) |
| Number of subjects with rationale: | The existing literature clearly documents MDCT as the gold standard for the detection of acute, spontaneous intracranial hemorrhage.^19^ Therefore the readings of the MDCT will be set as ground truth.  To calculate the sample size, hypothetical experiments were simulated. To account for variation, the diagnostic performance of hypothetical readers was varied around 99% for the sensitivity and around 98% for specificity. Rates were attributed randomly with equal chance. To represent “difficult cases”, i.e. patients who present with an isolated infratentorial hemorrhage we introduced a subpopulation of patients for whom the performance of raters was only 70% sensitivity. This subset was weighted in the final sample size calculations with 2 %.  Each sample size, n_i=1,..,19_ = 80,…,260 was evaluated by sampling 999 times n_i_ individual samples with a range of readers from 1 to 7.  If power is set at 90%, the number of readers at 6, and the drop-out rate at 5%, a total of **252 patients (**238 patients without drop-outs) must be recruited. The patients must be pre-selected in a ratio of hemorrhage positive to hemorrhage negative of 1:1, i.e., 126 patients are presenting with and 126 patients without intracranial hemorrhage. To ensure an enrollment in this ratio, a bucket design will be used. There will be three predefined buckets: (1) 126 acute ischemic (non-hemorrhagic) stroke patients, (2) 126 hemorrhagic stroke patients, which include (3) 14 patients with an isolated infratentorial or basal hemorrhage. |
| Duration of the investigation: | 36 months total  24 months enrollment period |
| Investigation schedule: | 25. October 2022: first patient-in (anticipated)  31. December 2024: last patient-out (anticipated) |
| Investigator(s): | [name]. [name]. (PI)  [name] [name], M.D. (Co-PI and US Chair) |
| Investigational site(s) | Multicentric (up to 30 sites)  Up to 30 sites in Switzerland, United States of America, France, Finland and Spain |
| Statistical  considerations: | The primary analysis will be based on the full analysis set.  A generalized linear random-effects model with a logit link function will be fit. From the fixed-effect intercept of sensitivity and specificity, the 95%-Cis will be calculated applying the method of Wald. Difficult cases will be weighted with 2%. Sensitivity will be calculated based on the results of all core-lab readers of the non-contrast FDCT scans of all patients for which the ground truth was deemed to be hemorrhage positive. Specificity will be calculated based on the results of all core-lab readers of the non-contrast FDCT scans of all patients for which the ground truth was deemed to be hemorrhage negative. It will be tested whether both the lower bound of the 95%-CI of the sensitivity and of the specificity is higher than the margin of 95%.  All results will be reported in concordance with the STARD guidelines.^20^ |
| Compliance statement: | This investigation will be conducted in compliance with the CIP, the current version of the Declaration of Helsinki, ISO14155, ICH-GCP (as far as applicable) as well as all national legal and regulatory requirements. |

# ABBREVIATIONS

ADE Adverse Device Effect

AE Adverse Event

AHA/ASA American Heart Association/American Stroke Association

AIS Acute ischemic stroke

ASADE Anticipated Serious Adverse Device Effect

ASR Annual Safety Report

CA Competent Authority (e.g., Swissmedic)

CEC Competent Ethics Committee

CI Confidence Interval

CIP Clinical investigation plan

ClinO Ordinance on Clinical Trials in Human Research

ClinO-MD Ordinance on Clinical Trials with Medical Devices

CRF Case Report Form (pCRF paper CRF; eCRF electronic CRF)

DD Device Deficiency

DSMC Data Safety Monitoring Committee

FAS Full Analyse Set

FDCT Flat Detector Computer Tomography (will be used as a synonym for non-contrast syngo DynaCT Sine Spin)

GLMM Generalized linear mixed model

Ho Null hypothesis

H1 Alternative hypothesis

HRA Federal Act on Research involving Human Beings

IB Investigator’s Brochure

ICF Informed Consent Form

ICH Intracranial Hemorrhage

ICH-GCP International Council for Harmonisation – guidelines of Good Clinical Practice

ICL Imaging Core Lab

IFU Instruction for Use

ISF Investigator Site File

ISO International Organisation for Standardisation

ITT Intention to treat

IRB Institutional Review Board

LAR Legally authorized representative

LVO Large Vessel Occlusion

NIHSS National Institute of Health Stroke Scale

MedDO Medical Devices Ordinance

MD Medical Device

MDCT Multi detector Computer Tomography

MDR Medical Device Regulation (EU) 2017/745 of 5 April 2017

OEM Original Equipment Manufacturer

PI Principal Investigator

SADE Serious Adverse Device Effect

SAE Serious Adverse Event

SADE Serious Adverse Device Effect

SAH Subarachnoid hemorrhage

SAP Statistical Analysis Plan

SDV Source Data Verification

SNCTP Swiss National Clinical Trials Portal

SOP Standard Operating Procedure

USADE Unanticipated Serious Adverse Device Effect

# INVESTIGATION SCHEDULE

| **Schedule of assessments** | | | |
| --- | --- | --- | --- |
| **Visits** | | **0** | **1** |
|  |  | **Screening and enrollment** | **Intervention** |
| **Assessment** | **Time Window** | Admission | 0 – 4 hours after Non-contrast MDCT scan |
|  | **Method** | Clinical Visit | Intervention |
| Informed consent | | X^1^ |  |
| Patient demographics (i.e. age, gender, pre-existing conditions) | | X |  |
| National Institute of Health Stroke Scale | | X |  |
| Pregnancy test (only in women of childbearing potential) | | X |  |
| Patient logistics (i.e. time from onset to admission / imaging) | | X |  |
| Medical history (including medication) | | X |  |
| Non-contrast MDCT head scan^2^ | | X |  |
| Enrollment | | X |  |
| Non-contrast syngo DynaCT Sine Spin FDCT head scan | |  | X |
| AEs | | Only if procedure related up to 24 hours after procedure | |
| SAEs | | Only if procedure related up to 24 hours after procedure | |

1. Post-hoc consent if patient was not able to give consent at trial inclusion (according to national and applicable law)

2. For clarification the MDCT scan could have been done in an external hospital (in case of transfer patients) if the images of the MDCT are available at the PACS of the enrolling hospital and the quality was deemed to be sufficient by the enrolling physician and all other in- and exclusion criteria are met

AEs Adverse Events, FDCT Flat-Detector CT, MDCT Multi-Detector CT, SAEs Serious Adverse Events

## 1.3 Principial Investigators (PIs) in Switzerland and abroad

Please find a comprehensive list of all participating investigators in Appendix A Principal Investigators.

Roles: responsible for the conduct of the investigation at their site

## 1.5 Laboratory

Not applicable

## 1.7 Data Safety Monitoring Committee (DSMC)

The DSMC is independent. None of the DSMC members will be involved in the enrollment of patients in this clinical investigation. This board shall provide recommendations to the Sponsor and Investigators regarding stopping/continuing enrolment in the clinical investigation. The DSMC role, reporting structure, meeting modalities etc. are defined and regulated in a separate DSMC charter. The DSMC will meet after enrollment of 25% (63 patients), 50% (126 patients), and 75% (189) of the patients. The DSMC consists of the following members:

[name] , M.D., PhD, MSc

Chairman of the Second Department of Neurology

National & Kapodistrian University of Athens,

[name]

[name]. [name]

Deputy Head of the Department of Medical Statistics

University Hospital Hamburg Eppendorf

[name]

[name], MD

Department of Neurosurgery

Jackson Memorial Hospital

[name]

## 1.8 Primary Imaging Core Lab (ICL)

The objectives of the primary ICL are to provide an unbiased assessment of several imaging measures. All assessments will be made according to a Core-Lab manual, which is written and finalized prior to any reading. They are knowledgeable in the analysis of neuroradiological images and will be blinded, i.e., unaware of the patient`s treatment allocation and the clinical investigation results. The ICL will receive de-identified imaging data only. ICL results will overrule site/investigator assessments. The qualified institution as ICL is:

Neurovascular Imaging Research Core

Director [name] [name], MD, FAAN, FAHA, FANA, FSVIN, FWSO

University of California LA

Los Angeles, California

United States of America (USA)

## 1.9 Secondary Imaging Core Lab (ICL)

The objective of the second ICL is to make a final ruling a) in case there is a disagreement in the clinical rating and the first core-lab rating of the MDCT or b) in case the majority of the first core-lab ratings (at least 5 out of 6) of the FDCT is hemorrhage positive and the ground truth is hemorrhage negative, to determine if the hemorrhage has occurred between both scans. The second ICL will be blinded to the rating of the core-lab 1 but not to the remaining clinical data. The second ICL defines the ground truth for all patients in whom the clinical rating and the rating of core-lab 1 of the MDCT are divergent (majority vote).

The second ICL will be performed by [name], MD (Head of the Clinic for diagnostic and interventional Neuroradiology, University Hospital Bern), who is an internationally known Neuroradiologist with more than 20 years of experience in the assessment of cranial non-contrast images in stroke patients. All readings will be done in accordance with a core-lab manual, which will be written prior to any assessment. As the second ICL will not be blinded to any data (except to the readings of the first ICL), it is not a problem that [name], MD might have been involved in the original enrollment of patients at the study site Inselspital Bern, Bern, Switzerland.

[name], MD

Head of the Clinic for diagnostical and interventional Neuroradiology

University Hospital Bern

[name]

[name]

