- Bucket 2 and 3 (haemorrhage patients) 126 patients including 14 patients in bucket 3 (isolated infratentorial or basal intracranial haemorrhage including perimesencephalic SAH)

Local investigators must keep a screening log.

The primary objective (sensitivity and specificity of non-contrast syngo DynaCT Sine Spin imaging for the detection of intracranial haemorrhage) will be assessed by blinded readers in an imaging core-lab. All readers will be blinded to all clinical characteristics and will not be involved in the treatment or enrolment of patients. Prior to the core-lab assessment all scans will be anonymized, reconstructed in a standardised way (fixed angles and slide sizes) and randomized. All readings will be noted on standardized forms.

The ground truth (i.e., if an intracranial haemorrhage is present or not) will be defined based only on the MDCT scans according to the following procedure: If the reading of the clinical reader (the enrolling physician at the participating site) and the reader from the first blinded core-lab (provided by the Neurovascular Imaging Research Core, [name], University of California LA, Los Angeles, California, USA) is consistent this will be deemed as ground truth. If they are inconsistent a second core-lab (provided by [name], Inselspital Bern, Bern, Switzerland) will make a final ruling (majority vote). The second core-lab can use all available clinical information but will be blinded to the results of the reading from core lab one. The following table illustrates the definition of the ground truth:

| Modality | Reader | Analysis |
| --- | --- | --- |
| MDCT | Clinical Reader | Agreement: ground truth |
|  | Core-Lab 1 | Disagreement: Unblinded expert reader in 2^nd^ corelab determines ground truth (majority vote) |

Table 1: Definition of the ground truth

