The FDCT readings of the six core-lab readers will be compared with the ground truth and based on this comparison they will be rated as true positive, true negative, false positive or false negative. This will be done separately for each reader. In case most of the first core-lab readers (at least 5 out of 6) detect a hemorrhage on the FDCT scan, which according to the ground truth was no present on the MDCT scan, the second core-lab will use all available images and clinical data (unblinded) to decide if there is any evidence for the hemorrhage to have occurred between the MDCT and FDCT scans (always a possibility in patients with a stroke, e.g., without a hemorrhage on MDCT, treated with iv-lysis and then with a hemorrhage on FDCT as a complication of intravenous lytic treatment). In this case the patient will be excluded from further analysis. See table 2 for a detailed overview of all possible constellations:

| Ground truth | Core-Lab 1 | Core-Lab 2 | Final Result |
| --- | --- | --- | --- |
| MDCT | FDCT | FDCT | FDCT |
| (+) | (+) | NA | True (+) |
| (-) | (-) | NA | True (-) |
| (+) | (-) | NA | False (-) |
| (-) | (+) | (-) | False (+) |
| (-) | (+) | (+) | Hemorrhage occurred between scans |

Table 2. Overview of possible outcomes for the FDCT readings

Based on the results the sensitivity and specificity of non-contrast syngo DynaCT Sine Spin for the detection of hemorrhages will be calculated.

We chose this design approach for the following reasons:

1. The only way to benchmark the diagnostic performance of non-contrast syngo DynaCT Sine Spin imaging for the detection of intracranial haemorrhage is to compare it to the gold standard, which is cranial non-contrast MDCT imaging.^19, 44^ Therefore, it is of pivotal importance that scans of the same person, which were acquired under comparable conditions are used. This is ensured by the facts that (a) only patients in whom no invasive procedure between both scans is planned can be enrolled and (b) that the time period between both scans is under four hours. Using these criteria, it is highly unlikely, that new bleeding events occur between both scans. However, to account for the very low possibility of an early bleeding due to intravenous lysis, which would occur after the MDCT but before the FDCT, a second core-lab was implemented to identify these cases.

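### When MDCT readings disagree, nothing in the protocol keeps the study FDCT from the second core lab, so the index test may inform its own reference standard

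*Protocol*

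**What the plan says.** Each FDCT reading is scored as true or false against a ground truth. Section 6.1 introduces it so: "The ground truth (i.e., if an intracranial haemorrhage is present or not) will be defined based only on the MDCT scans". If the site's clinical reader (the enrolling physician) and core-lab 1 agree on the MDCT, their common reading stands. If they disagree, section 1.9 makes the second core lab's ruling the ground truth.

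What the second core lab may see is described in several ways:

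- Synopsis: the adjudicator "will read the MDCT scan and review all available clinical data".
- Section 6.1: "The second core-lab can use all available clinical information but will be blinded to the results of the reading from core lab one". The table that follows calls this person an unblinded expert reader.
- Section 1.9, explaining why involvement in enrolment at one site is acceptable: "the second ICL will not be blinded to any data (except to the readings of the first ICL".

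The same core lab has a second task. It arises if at least five of six FDCT readers call a hemorrhage in a patient whose ground truth is negative, and it asks whether the bleed is new since the MDCT. Under section 6.1, "the second core-lab will use all available images and clinical data (unblinded) to decide if there is any evidence for the hemorrhage to have occurred".

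Section 1.8 adds a general rule for the primary core lab: "ICL results will overrule site/investigator assessments".

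**The concern.** A reference standard should be set without knowledge of the test being evaluated. If the adjudicator has seen the FDCT, a ruling on an unclear MDCT can lean towards what the FDCT shows. Ground truth and index test then agree partly by construction (incorporation bias).

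The patients exposed are those whose MDCT was read differently by two people. They are likely the subtle bleeds and mimics, where FDCT errors would also be expected. The success criterion tolerates few errors: section 11.1 requires both lower 95% bounds, for sensitivity and for specificity, to exceed 95%.

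Two related points weaken the independence of the ruling. Section 1.9 accepts that the adjudicator may have helped enrol patients at one site, while section 6.1 makes the enrolling physician the clinical reader. And the general rule in section 1.8, read literally, would settle a site/core-lab disagreement without any adjudication.

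**Working it through.** **Is the FDCT excluded when ground truth is set?**

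1. Section 6.1 names the MDCT as the only basis, but the sentence continues: the ground truth "will be defined based only on the MDCT scans according to the following procedure". That procedure admits all clinical information for discordant cases. So the restriction to MDCT is already loosened within the same paragraph.
2. The Synopsis and section 6.1 speak of clinical data. Neither says whether a local FDCT report belongs to it. Section 2 describes the Sine Spin scan as routine in most subjects, and section 12.1.2 lists FDCT images and radiology reports among the source documents, so such a report may exist.
3. Section 1.9 has the widest wording. Its single exception covers core-lab 1's readings. That hides the six FDCT ratings, but not the FDCT images or a local report.
4. Section 12.6 keeps scans of both modalities on one server and makes images available to the second core lab for some participants, without separating its two tasks.
5. Section 9.2 repeats the adjudication rule and adds no restriction.

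No section excludes the FDCT in this role. No section says that it is supplied either.

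**How many patients could matter?** The protocol gives no figure for this, so what follows is an illustration.

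*Inputs (section 11.2):* 238 evaluable patients, allocated 1:1, so 119 per group; six readers; 5% drop-out; 2% total weight for 14 difficult cases. The plan's total reproduces per group: 119/0.95 = 125.3, rounded up to 126, and 2 × 126 = 252. The simulated 238 was not re-run, because the assumed correlation between readers is not given as a number.

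*Extreme A: all six readers always agree, so the patient is the unit (n = 119).* The Clopper-Pearson lower bound with x errors is the 2.5% quantile of Beta(119 − x, x + 1). The logit-Wald bound is expit{ln[(119 − x)/x] − 1.96·√[1/(119 − x) + 1/x]}.

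| Errors | Clopper-Pearson | Logit-Wald |
|---|---|---|
| 0 | 96.95% | not defined |
| 1 | 95.41% | 94.28% |
| 2 | 94.06% | 93.53% |

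The exact bound crosses 95% between one and two patients. The logit-Wald bound, closer in form to the planned interval, is already below 95% at one.

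*Extreme B: all 119 × 6 = 714 ratings independent.* The logit-Wald bound is 95.03% with 24 errors and 94.87% with 25. Since 24/6 = 4, this corresponds to about four patients misread by every reader.

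*Weighting (sensitivity only).* In a simple weighted proportion, with all 14 difficult cases evaluable, each carries 0.02/14 = 0.14 percentage points. Each of the other 105 bleeds carries 0.98/105 = 0.93. A disputed infratentorial case therefore has roughly one-sixth to one-seventh of the influence.

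*Number adjudicated.* If 2% to 5% of MDCT readings were discordant (an assumption), 252 × 0.02 = 5 to 252 × 0.05 = 12.6, about 13 patients, would be adjudicated. This is a ceiling: the FDCT must also have changed the ruling.

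**The case against.** The strongest reply is that the protocol words the two tasks differently. For the MDCT ruling it speaks of the MDCT and clinical data; only for the between-scan question does it add all available images. The broad phrase in section 1.9 comes from a sentence defending the adjudicator's site involvement and was perhaps never meant as an access rule. A core-lab manual, not shown here, may restrict access. This stands to the extent that FDCT access is inferred. It does not close the gap, because section 1.9 reads the other way and nothing in the protocol excludes the FDCT.

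Second, the adjudicator only breaks a tie between two readings made without the FDCT. The site's classification is entered at enrolment, which precedes the FDCT (Synopsis, section 6.2.3), and the core-lab MDCT reader is separate from the FDCT readers (sections 6.2.2 and 11.3). This stands: the final label always matches one FDCT-independent reading, and concordant patients are untouched.

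Third, a reader might infer that both sensitivity and specificity are necessarily inflated. The documents do not support that. The bias is favourable only where the adjudicator's view of the FDCT matches the six readers' ratings. An expert without the 90-second limit who saw a bleed that the readers missed could rule positive, which would create false negatives and lower sensitivity.

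Fourth, the binomial bounds are not the planned analysis, which is a mixed logistic model with crossed reader and patient effects and down-weighted difficult cases. This also stands; they show leverage only.

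On the side points, section 1.9 says only that the adjudicator might have been involved in enrolment, at one of up to 30 sites. And the adjudication rule is stated consistently in the Synopsis and sections 1.9, 6.1 and 9.2, against one general sentence in section 1.8.

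**Conclusion.** The point holds as a gap and an inconsistency that should be closed before adjudication begins. Section 6.1 promises an MDCT-only ground truth. For discordant MDCT readings, section 1.9 leaves the adjudicator blinded to nothing except core-lab 1's readings, and no section withholds the study FDCT or its report. The index test may therefore inform the reference standard in those patients.

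The expected tendency is towards agreement between FDCT and ground truth, but direction and size cannot be fixed because the discordance rate is not given. Between one and about four wholly misread patients could matter to a 95% lower bound. That range assumes 119 patients per group and runs from perfect reader agreement to independent ratings; an infratentorial case counts for much less.

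A reader might go further and infer that the adjudicator is in fact shown the FDCT, that one or two realigned patients would decide the trial, or that one person's reading is counted twice in the majority vote. None of these is established. The first is not stated anywhere, the second depends on the model, reader correlation and weighting, and the third requires the adjudicator personally to have been the clinical reader.

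**What to change.** - State in section 1.9, section 6.1, section 9.2 and the Synopsis that, when ruling on MDCT ground truth, the second core lab sees the MDCT and the clinical data but not the study FDCT images or any FDCT report.
- Require that this ruling be recorded and locked before the FDCT is released for the separate between-scan question. Referral for that question in itself reveals that at least five of six readers called the FDCT positive.
- State that the adjudicator does not rule on a patient for whom that person was the site's clinical reader, and say in advance what happens instead, for example that core-lab 1's reading stands.
- Reconcile the sentence in section 1.8 with the adjudication rule, by limiting it to other items or deleting it.
- Mirror these rules in the core-lab manual.

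The cost is a wording change and some handling to keep FDCT reports out of the adjudication package for the disputed cases. There are no extra scans, patients or reads, and the sample size is unchanged.
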